## 1.0 Abbreviations

|          |                                                                |
|----------|----------------------------------------------------------------|
| ACR      | American College of Rheumatology                               |
| ACPA     | Anti-Citrullinated Peptide Antibody                            |
| AS       | Ankylosing spondylitis                                         |
| bDMARD   | Biological Disease-Modifying Anti-Rheumatic Drug               |
| csDMARD  | Conventional Synthetic Disease-Modifying Anti-Rheumatic Drug   |
| CDAI     | Clinical Disease Activity Index                                |
| CI       | Confidence Interval                                            |
| CRF      | Case Report Form                                               |
| CRP      | C-Reactive Protein                                             |
| DAS28    | Disease Activity Score, 28 joints                              |
| DMARD    | Disease-Modifying Anti-Rheumatic Drug                          |
| DMARD-IR | Disease-Modifying Anti-Rheumatic Drug -Inadequate Responder    |
| eCRF     | Electronic Case Report Form                                    |
| EGA      | Evaluator (physician) Global Assessment of disease activity    |
| eHEALS   | Electronic Health Literacy Scale                               |
| ESR      | Erythrocyte Sedimentation Rate                                 |
| EULAR    | European League Against Rheumatism                             |
| FACIT-F  | Functional Assessment of Chronic Illness Therapy-Fatigue Scale |
| GCP      | Good Clinical Practice                                         |
| GEP      | Good Epidemiological Practice                                  |
| HAQ-DI   | Health Assessment Questionnaire Disability Index               |
| HCP      | Health Care Professional                                       |
| HRQOL    | Health Related Quality of Life                                 |
| HRU      | Health care resource utilization                               |
| IL-6     | Interleukin-6                                                  |
| IMID     | Immune-mediated Inflammatory Disease                           |
| IR       | Inadequate Responder                                           |
| IV       | Intravenous                                                    |
| JAK      | Janus Kinase                                                   |
| MCS      | Mental Component Score                                         |

---

|          |                                                                    |
|----------|--------------------------------------------------------------------|
| MDGA     | Medical Doctor Global Assessment (Physician Global Assessment)     |
| mm       | Millimeter                                                         |
| MTX      | Methotrexate                                                       |
| MEDRA    | Medical Dictionary for Regulatory Activities                       |
| NRS      | Numerical Rating Scale                                             |
| OR       | Odds Ratio                                                         |
| PCS      | Physical Component Score                                           |
| PGA      | Patient Global Assessment of disease activity                      |
| PMOS     | Post-Marketing Observational Study                                 |
| PRO      | Patient Reported Outcome                                           |
| PSP      | Patient Support Program                                            |
| RA       | Rheumatoid arthritis                                               |
| RF       | Rheumatoid Factor                                                  |
| SAP      | Statistical Analysis Plan                                          |
| SDAI     | Simple Disease Activity Index                                      |
| SC       | Subcutaneous                                                       |
| SF-36v2  | 36-Item Short Form Health Survey, Version 2.0                      |
| SJC      | Swollen Joint Count                                                |
| TAI      | Total Activity Impairment                                          |
| TJC      | Tender Joint Count                                                 |
| TNF      | Tumor Necrosis Factor                                              |
| TNFi     | Tumor Necrosis Factor Inhibitor                                    |
| TSQM     | Treatment Satisfaction Questionnaire for Medication                |
| tsDMARD  | Targeted Synthetic Disease-Modifying Anti-Rheumatic Drug           |
| TWPI     | Total Work Productivity Impairment                                 |
| UC       | Ulcerative Colitis                                                 |
| VAS      | Visual Analogue Scale                                              |
| WPAI     | Work Productivity and Activity Impairment                          |
| WPAI-RA  | Work Productivity and Activity Impairment, Rheumatoid Arthritis    |
| WPAI-GH  | Work Productivity and Activity Impairment, General Health          |
| WPAI-SHP | Work Productivity and Activity Impairment, Specific Health Problem |

---

### 3.0

### Abstract

**Title:** Cross-sectional Study Evaluating patient satisfaction, adherence features, and their association with socio-demographic and clinical characteristics of DMARD-inadequate responder rheumatoid arthritis patients - SENSE

#### Background

Rheumatoid arthritis (RA), if not controlled properly, may result in severe and progressive articular damage, loss of function, deterioration of the quality of life, and increased mortality. Despite the wide range of treatment options, many patients with RA remain sub-optimally managed and sustained remission is rarely achieved.

Low adherence rate is a serious medical problem in RA and represents a significant financial burden to health care and society. Suboptimal disease control in RA could be a result of low medication adherence. Satisfaction with medication attributes has been found to affect patients' dosing adherence and persistence with treatment over time.

Although patient satisfaction is a useful and essential outcome to assess, patient satisfaction in patients not responding to their current therapies is not well examined. Identifying areas lacking satisfaction in the group of patients with inadequate treatment response, thus candidates for treatment regimen modification, can guide the future treatment decision. In addition to sub-optimal RA control assessed by traditional clinical measures, patients' needs remain frequently unmet across key patient reported outcome (PRO) domains such as pain, physical function, mental function, and fatigue, which can all adversely affect their adherence, social function, sexual function, the ability to work, and overall well-being.

#### Rationale

There is a need for better and in-depth understanding the clinical, socio-demographic, health-economic, adherence and PRO characteristics of RA patients with inadequate response to currently available DMARDs. Moreover, in the same sub-optimally controlled RA population, additional data are necessary about their treatment satisfaction, expectations and treatment preferences for RA. Evaluating differences in the above listed areas across subgroups of patients treated with different treatment modalities and regimes, route of RA treatment administration, clinical, demographic and PRO characteristics can guide personalized treatment, support shared treatment decision making and help achieve better disease outcomes in RA. Data collected in the study can also support the development of effective tools for improving adherence and may inform the optimal design of future patient support programs. Results will also inform about the current treatment strategies used in the management of the sub optimally controlled RA population.

#### Research Question and Objectives:

**Primary Objective:** To assess treatment satisfaction of patients with sub optimally controlled RA treated with conventional/targeted synthetic or biological DMARDs.

Definition of sub optimally controlled RA: moderate to high disease activity as measured by DAS28.

#### Secondary Objectives:

- To assess sociodemographic, clinical, functional, adherence and quality of life characteristics of sub optimally controlled RA patients treated with conventional/targeted synthetic or biological DMARDs.
- To assess healthcare resource utilization during 12 months prior to enrollment to the study in sub optimally controlled RA patients treated with conventional/targeted synthetic or biological DMARDs.
- To assess electronic health literacy of sub optimally controlled RA patients treated with conventional/targeted synthetic or biological DMARDs.
- To assess expectations towards RA therapy, medication preferences and needs for patient support of sub optimally controlled RA patients treated with conventional/targeted synthetic or biological DMARDs
- To determine relationship between treatment satisfaction, its subdomains and patient characteristics.
- To determine relationship between adherence and patient characteristics.
- To determine relationship between medication preferences and patient characteristics.
- To determine relationship between treatment expectations and patient characteristics.
- To determine relationship between specific PSP-related needs and patient characteristics.
- To evaluate the above measures in various subgroups of patients stratified by treatment modalities used, by clinical characteristics, by presence of comorbidities, if there are sufficient patients in each subgroup.

To understand treating rheumatologists treatment strategy in the study population and its relationship with patient characteristics.

**Study Design:** Multi-country, multicenter, cross-sectional non-interventional study.

**Data Analysis:**

Data from all clinical assessments of the patients will be summarized using summary statistics. Additional exploratory analyses may be added on a data driven basis and will be specified in SAP. Separate analysis is planned for each country based on the needs of the particular participating country.

Statistical analysis in general will include: descriptive statistics, comparative subgroup analysis, relationship between variables and predictive models. Detailed statistical analysis plan (SAP) will be provided separately.

## 4.0 Amendments

| Number | Date          | Section of Study Protocol       | Amendment or Update | Reason                                                                                                                                                                                                                                              |
|--------|---------------|---------------------------------|---------------------|-----------------------------------------------------------------------------------------------------------------------------------------------------------------------------------------------------------------------------------------------------|
| 1      | 18 March 2019 | 5.0
9.1
9.3
Appendix 1 | Amendment           | 
 
• Modify study milestones
 
• Removal of copyright protected PRO questionnaires from the Appendix
 
• Modify sample size
 
• Correct typos
 
 
See Appendix 7 for details
 |

## 5.0 Milestones

Major study milestones and their planned dates are as follows:

|                                |                   |
|--------------------------------|-------------------|
| Start of Data Collection:      | 02 September 2018 |
| End of Data Collection:        | 31 May 2019       |
| Final Report of Study Results: | 01 December 2019  |

## 6.0 Rationale and Background

### 6.1 Background

Rheumatoid arthritis (RA) is a chronic inflammatory disease which, if not controlled properly, may result in severe and progressive articular injury, loss of function, deterioration of the quality of life, and increased mortality [1-4]. Biological disease modifying drugs (bDMARDs) are typically used as second-line therapy in patients with an inadequate response to conventional synthetic disease modifying drugs (csDMARDs). The group of targeted synthetic DMARDs (tsDMARDs) represents a novel therapeutic option for patients with inadequate response to cs/bDMARDs [13-22]. However, the role of tsDMARDs in current treatment paradigm is not yet fully established, partially since we still have limited data on their real-world effectiveness and on the factors associated with sub-optimal response to them [23].

Despite the fact that the range of treatment options is steadily increasing and RA therapies help to slow down disease progression and the development of joint damage, many patients with RA remain sub-optimally managed with sustained remission rarely achieved [5-11]. Two-thirds of RA patients do not respond adequately to their initial bDMARD, and sustained clinical remission is achieved in only 20–40% of patients treated with DMARDs [5, 6]. Moreover, radiographic progression can still occur even in the presence of clinical remission [12]. Suboptimal management of RA results in increased healthcare resource use and medical costs [9].

**Treatment adherence** is of particular importance in RA as it is characterized by fluctuating and usually progressive disease courses and a need for lifetime management [27-32]. Despite the fact that the efficacy of available medications is proven even with long term use [37-39], the level of adherence is still suboptimal among RA patients, varying from 30 to 80% [4,33], thus resulting in suboptimal outcomes and representing a significant financial burden to health care [34-36,42-43]. There is evidence available confirming that bDMARD use is associated with better adherence than conventional oral DMARDs in RA [40].

**Patients' satisfaction** with therapy is associated with the level adherence and treatment choice [44]. Measuring satisfaction can cover various areas, e.g. evaluation of the acceptability of care or treatments; comparison of health-care programs or treatment options; identification of service or treatment approaches that require change; and screening of patients who are likely to become non-adherent to care plans or medication regimens [44]. Therefore, patient satisfaction is a useful outcome measure for evaluating the benefit of patient support programs, services and products, and can inform development of products, services and devices [45-47, 51-54]. Satisfaction is also closely linked to patients' **treatment expectations** mainly related to their everyday life, personal concerns, level of pain, and sometimes there is a disconnection between clinicians' and patient's treatment goals [52]. In order to have better adherence and disease outcomes, treating physicians have to better understand patient expectations [50, 53, 54].

Identifying areas lacking satisfaction (e.g. related to convenience or tolerability) in the group of RA patients with inadequate treatment response, thus candidates for treatment regimen modification, can guide the future treatment decision. The subsequent treatment regimen based on the identified areas with low satisfaction, in line with patient preferences will be more likely associated with higher willingness to adhere to prescription, which will ultimately lead to higher real-life efficacy [39].

As shown by a recently published literature review [78], despite the wide array of available treatments for RA, clinical and patients' needs remain unmet across key patient related outcome (PRO) domains such as pain, physical function, mental function, and fatigue, which can all adversely affect adherence, social function, sexual function, the ability to work, and overall well-being [79]. This supports the trend for more patient-centered care, better doctor–patient communication and shared decision-making [54–59], ultimately improving the quality of care, as an overarching principle recommended by EULAR [23]. Among PROs, **fatigue** in RA is of particular interest [60] since it has been consistently shown to be important for patients with RA [61], having consequences on all aspects of quality of life [62]. Results from independent studies highlight that **joint stiffness** is also an important feature of RA [63], and its level reflect functional disability and pain more than traditional markers of inflammation [64]. Similarly, people with RA identify **joint pain** as their most important symptom, one that often persists despite optimal control of inflammatory disease [52, 65], thus non-inflammatory components of RA pain should be considered when gauging eligibility for or response to RA therapies [65].

## 6.2 Rationale

There is a need for better and in-depth understanding the clinical, socio-demographic, health-economic, adherence and PRO characteristics of RA patients with inadequate response to currently available DMARDs.

Moreover, in the same sub-optimally controlled RA population, additional data are necessary about their treatment satisfaction, expectations and treatment preferences for RA.

Evaluating differences in the above listed areas across subgroups of patients treated with different treatment modalities and regimes, route of RA treatment administration, clinical, demographic and PRO characteristics can guide personalized treatment, support shared treatment decision making and help achieve better disease outcomes in RA.

Data collected in the study can also support the development of effective tools for improving adherence and may inform the optimal design of future patient support programs.

Results will also inform about the current treatment strategies used in the management of the sub optimally controlled RA population.

## 7.0 Research Question and Objectives

The research question is as follows: what are the clinical, socio-demographic, workability, healthcare resource utilization characteristics, treatment satisfaction, preferences and residual unmet needs of

patients with inadequate response to their current RA treatment with conventional/targeted synthetic or biological DMARDs?

## 7.1 Primary Objective

The primary objective of the study is to assess treatment satisfaction of patients with sub optimally controlled RA, treated with conventional/targeted synthetic or biological DMARDs.

Definition of sub optimally controlled RA: moderate to high disease activity as measured by DAS28.

## 7.2 Secondary Objectives

- To assess the sociodemographic, clinical, functional, adherence and quality of life characteristics of sub optimally controlled RA patients treated with conventional/targeted synthetic or biological DMARDs.
- To assess healthcare resource utilization (HRU) during 12 months prior to enrollment to the study in sub optimally controlled RA patients treated with conventional/targeted synthetic or biological DMARDs.
- To assess electronic health literacy of sub optimally controlled RA patients treated with conventional/targeted synthetic or biological DMARDs.
- To assess expectations towards RA therapy, medication preferences and needs for patient support of sub optimally controlled RA patients treated with conventional/targeted synthetic or biological DMARDs
- To determine relationship between treatment satisfaction, its subdomains and patient characteristics.
- To determine relationship between adherence and patient characteristics.
- To determine relationship between medication preferences and patient characteristics.
- To determine relationship between treatment expectations and patient characteristics.
- To determine relationship between specific PSP-related needs and patient characteristics.
- To evaluate subgroups of patients, if there are sufficient patients in each subgroups:

- To evaluate the above measures in the subgroups of patients treated with different treatment modalities, regimes and line therapy and route of administration (e.g. patients treated with csDMARDs, bDMARDs, tsDMARDs; patients treated with orally or parenterally administered DMARDs (SC or IV), patients treated in monotherapy, patients treated with combination therapy, patients treated with first or second line bDMARD).
- To evaluate the above measures in subgroups of patients with different clinical characteristics (e.g. with high or moderate disease activity).
- To evaluate the above measures between the subgroups of patients with and without comorbidities including cardiovascular comorbidities.
- To understand treating rheumatologists' treatment strategy in the study population and its relationship with patient characteristics.

## **8.0 Research Methods**

### **8.1 Study Design**

This is a multi-country, multi-center, cross-sectional, non-interventional study. The data collection period will be approximately 9 months. Each patient attends a single study visit.

#### **The following data will be collected:**

1. Demographic data: age, gender, race, occupation, education, place of living (rural/urban)
2. RA disease related data
  - Year of RA diagnosis
  - Diagnostic criteria used for RA diagnosis
  - Current disease activity measured by DAS28 and SDAI/CDAI
  - Imaging results: Presence/absence of structural damage by X-ray (X-ray assessment not older than 6 months from enrollment is acceptable)
  - Laboratory tests: rheumatoid factor (RF) (not older than 3 months from enrollment), anti-citrullinated protein antibody (ACPA) (not older than 3 months from enrollment), current CRP

- Current co-morbidities (including but not restricted to metabolic, cardiovascular, mental, endocrine diseases according latest version of MeDRA)

3. Medication related data

- Prior and current treatment for RA
- Current concomitant medication for comorbidities
- Treatment strategy of treating rheumatologists: whether there is a plan for switching to a different DMARD (Yes / No); in case of plan to switch: mode of action of next DMARD.

4. Health care resource utilization (HRU) in the past 3 months from enrollment.

5. Patient reported outcomes

- Current physical function measured by HAQ-DI
- Level of fatigue measured by FACIT-F
- Duration and severity of morning stiffness measured by VAS
- Level of worst joint pain measured by VAS
- Satisfaction with current treatment for RA measured by TSQM version 1.4
- Self-reported adherence measured by 0-100 mm VAS
- Workability measured by WPAI-RA
- Quality of life health assessment measured by SF-36v2
- Assessments on electronic health literacy by eHEALS
- Questionnaires to assess patient needs for support via PSP, medication preferences and treatment expectations

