## 9.0 Setting

As this is an observational, non-interventional study, patient's treatments are determined solely by the treating physician, which falls within the scope of the physician's/institution's general liability insurance coverage and precedes the decision to offer the patient the opportunity to participate in the study.

According to the requirements for non-interventional or observational studies, no additional diagnostic or monitoring procedures will be applied to the patients included in the study other than those which would ordinarily be applied in the course of the particular therapeutic strategy.

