## **9.2 Data Sources**

Data for this study will be collected during a single visit previously scheduled for a routine follow-up of the RA disease.

Data for relevant medical history will be obtained from patient charts and/or documentation.

Local language patient questionnaires will be used for assessing various PROs, treatment expectations, patient needs and preferences. Questionnaires listed in Appendices indicate the version used for the validated translations; specific country versioning may vary depending on the translation process.

Health care resource utilization (HRU) will be assessed using patient documentation and patient interview.

Only data which are part of routine will be collected, except PRO questionnaires which are not deemed as an intervention and are inherent part of epidemiological studies.

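### The 3-month limit on RF and ACPA, in a study confined to routine tests, shuts out serology results that are already in the chart

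*Protocol*

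**What the plan says.** All of this is in the Protocol.

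- **Section 8.1, list of data to be collected.** Among the laboratory tests, RF is limited by "rheumatoid factor (RF) (not older than 3 months from enrollment", and the next item reads "anti-citrullinated protein antibody (ACPA) (not older than 3 months from enrollment), current CRP". For structural damage, "X-ray assessment not older than 6 months from enrollment is acceptable".
- **Section 8.1, design.** "Each patient attends a single study visit".
- **Section 9.0.** "no additional diagnostic or monitoring procedures will be applied to the patients included in the study other than those which would ordinarily be applied" as part of the patient's treatment.
- **Section 9.2.** "Only data which are part of routine will be collected, except PRO questionnaires". The same section names charts as a source: "Data for relevant medical history will be obtained from patient charts and/or documentation".
- **Section 9.5.3.** Patient demographics and clinical characteristics are the candidate predictors in the multivariate linear and logistic models, with stepwise selection. RF and ACPA are not named there.

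Nothing in the Protocol provides for recording an RF or ACPA result older than 3 months, with or without its date, or says what to enter when no result falls in the window.

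**The concern.** RF and ACPA sit in section 8.1 next to items that characterise the disease, such as year of diagnosis and diagnostic criteria, for which no age limit is set. The eligibility criteria in section 9.0 do not restrict disease duration, so patients whose serology was established long before enrollment can be included. For such a patient the result may be in a chart that the site is already reading, yet the window excludes it, and the study adds no test to replace it.

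The loss occurs at data collection. An SAP can choose how to handle missing values, but it cannot recover a result that sites were told not to enter. Whether a value is missing would depend on how often each clinic repeats serology, across 100 sites in about 20 countries, so missingness at random is hard to assume. At stake are the description of serostatus in the study population and, if serostatus is offered as a predictor, the relationship analyses for satisfaction, adherence, preferences, expectations, support needs and planned DMARD switching.

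**Working it through.** **Step 1: put the rules together.** For one patient there are three cases.

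1. RF/ACPA was measured in routine care within the 3 months before enrollment: recorded.
2. RF/ACPA is ordinarily measured at the routine visit itself: recorded, because sections 9.0 and 9.2 allow it.
3. The last RF/ACPA is older than 3 months and routine care does not repeat it: the old result is outside the window, the study adds no test, and there is no second visit. The value is missing although it is on file.

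Only case 3 is a problem. Its frequency is not in the documents.

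**Step 2: reproduce the Protocol's own precision figures (section 9.3).** Inputs: SD 20 for TSQM global satisfaction and the stated sample sizes. Formula: t(0.975, n−1) × 20 / √n.

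| n | Computed | Stated |
|---|---|---|
| 1500 | 1.013 | 1.01 |
| 50 | 5.684 | 5.68 |
| 30 | 7.468 | 7.47 |
| 200 | 2.789 | 2.79 |

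All four reproduce. They concern the mean in all patients and do not depend on serology.

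**Step 3: illustrate the loss of precision.** Assumptions that are not in the documents: the share of patients with an admissible result (100%, 50%, 25%) and a 70/30 split of seropositive to seronegative. From section 9.3: N = 1500 and SD 20.

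Half-width of the 95% CI for a difference in mean satisfaction by serostatus: 1.96 × 20 × √(1/(0.7n) + 1/(0.3n)).

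- n = 1500: 39.2 × √(1/1050 + 1/450) = 2.21
- n = 750: 39.2 × √(1/525 + 1/225) = 3.12
- n = 375: 39.2 × √(1/262.5 + 1/112.5) = 4.42

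Half-width for a seropositive proportion near 50%: 1.96 × √(0.25/n).

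- n = 1500: 2.5 percentage points
- n = 750: 3.6 points
- n = 375: 5.1 points

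Halving the available results widens any such interval by √2 = 1.41, and keeping a quarter doubles it, whatever split is assumed. Possible selection bias cannot be put into figures from the documents.

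**The case against.** - **Tests are not forbidden outright.** A reader might infer from "no additional diagnostic or monitoring procedures will be applied to the patients included in the study" that no test can be done. The sentence goes on to exempt procedures ordinarily applied. Patients come to a routine visit after 1 to 4 months of moderate or high disease activity, and serology done routinely in that period counts. This stands: the loss is confined to patients whose serology is not routinely repeated.
- **The X-ray window might seem open to the same criticism.** It is not. The item recorded is whether structural damage is present or absent, and section 6.1 describes articular injury as progressive and says radiographic progression can occur even in clinical remission. An older film without damage may be out of date at enrollment, so a recency limit is defensible.
- **That older serology is still informative is a clinical judgement.** The Protocol does not address it, and a recency window can be defended in a cross-sectional study. This stands as a reason to keep the date and the flag. It is not a reason to leave the result unrecorded.
- **The harm to the models is conditional.** RF and ACPA are not named among the secondary variables, the subgroups or the predictors, and no complete-case analysis is specified. A reader might infer that the regressions will be run on re-tested patients only; the Protocol does not say so, and missing-data handling may be set in the SAP.
- **The figures are hypothetical.** The availability shares and the 70/30 split are assumed, and the Protocol does not specify a comparison of satisfaction by serostatus. Nothing shows that a large loss would occur.

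**Conclusion.** The point holds for RF and ACPA as a minor weakness in data collection. Read together, sections 8.1, 9.0 and 9.2 leave no way to record a chart result older than 3 months, and a value not collected cannot be restored in the analysis. How many patients this affects is unknown. The widening from 2.21 to 3.12 or 4.42 shows what would follow if half or a quarter of patients had an admissible result, under the assumed 70/30 split and SD 20; it is not a forecast. Any selection towards recently re-tested patients depends on serostatus being used in the secondary analyses and on how missing values are handled.

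The provisions can all be followed at once, so this is not a contradiction in the Protocol. RF and ACPA are not stand-alone eligibility criteria, and the primary endpoint, the TSQM satisfaction score in the full population, is unaffected.

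**What to change.** In section 8.1 and the eCRF, ask for the most recent RF and ACPA result in the chart, whatever its age, together with its test date. Derive a flag for results older than 3 months. Use all dated results in the main secondary analyses and repeat them on the in-window results as a sensitivity analysis. Keep CRP as a current value, and leave the 6-month X-ray window as it is.

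The cost is one date field per test and a short edit to the protocol text. Some recorded results will be older, but the date shows which. No procedure is added, so the study stays within sections 9.0 and 9.2. Everything the present rule would collect is still collected, and anyone who prefers the 3-month window can apply it in the analysis.
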